#### Predictors of Post-stroke Depression and Anxiety

##### Symptomatic components of mental disorders

Diagnosis of post-stroke psychological disorders is scrambled because of physical, somatic, vegetative, autonomic and cognitive signs of stroke that can forge or hide depressive or anxious symptoms (Spalletta et al., 2005; McGinnes, 2009; Carota and Bogousslavsky, 2012; Idiaquez et al., 2015).

Specific and reliable symptoms are needed to be defined in order to improve PSD and PSA diagnoses and treatment. In general stroke populations (including patients with motor and cognitive impairment) symptoms such as sadness, crying behaviors, negative thoughts and emotional reactivity during the acute phase predict the later levels of depression, whereas symptoms such as fatigue, apathy and concentration difficulties do not (Carota et al., 2005; Sibon et al., 2012; Lerdal and Gay, 2013). It would be relevant to explore if similar patterns could be found in minor stroke survivors on one hand, and it is important to replicate such studies in regard of post-stroke anxiety on the other hand.

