#### Content of EMA Questionnaires

Questionnaire 1 presents situation and context (multiple choice list): place, company, activity.

Questionnaire 2 – depression and anxiety symptoms (7 points Likert scale): sadness, anhedonia, fatigue, diminished concentration ability, negative thoughts on oneself, pessimism, anxiety, psychomotor agitation, physical tension, irritability.

Questionnaire 3 is related to positive and negative events that happened in the hours before the prompt: category of the most positive event and evaluation of the positive degree of this event on a 7-points Likert scale; category of the most negative event and evaluation of the negative degree of this event on a 7-points Likert scale; description of the reaction when confronted to this negative event. Fourteen sentences are answered by “yes” or “no” if they describe or not the behavior for coping with the situation.

Ecological Momentary Assessment questionnaires are explained and practiced with research staff at home when the first week of EMA begins. Then the procedure is reminded at the beginning of each week of EMA. All participants are contacted after 2 days during each EMA week to resolve any questions or difficulties.

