#### Data Analysis

##### Outcomes and statistical methods for primary objectives

Feasibility and acceptability of the EMA method will be assessed by examination of acceptance and compliance rate, fatigue effects and reactivity to assessment: completion rate during each week, participation at follow-up weeks (phases 2 and 3), missing data and assessment duration across time during each phase. Descriptive analysis will be performed to describe feasibility and acceptability. Compliance will be assessed as the completion rate of EMA questionnaires. This rate will be calculated as the ratio of completed questionnaires to all sent questionnaires within each phase (four questionnaires per day during 7 days for each participant). Follow-up participation will be the ratio of number of participants at phase 2 and 3 to the number of participants at inclusion (phase 1). Fatigue effect will be calculated as the evolution of the within-day mean of missing data. Reactivity to EMA assessment will be estimated by comparing anxiety, depression and quality of life scores (self-reported questionnaires and clinicians’ ratings) of EMA participants to other participants (not involved in the EMA part of the study, more information is given in the limitations section below).

Validity of the method will be examined by using three different EMA indexes consisting in different aggregation of anxious and depressive symptoms assessed with EMA for each participant: a global anxiety and depression index (including all 11 symptoms assessed), a specific depression index (including sadness, anhedonia, fatigue, concentration difficulties, negative thoughts, pessimism) and a specific anxiety index (including anxiety, agitation, physical tension, irritability, concentration difficulties).

Validity will be assessed by using Pearson correlations between EMA indexes with self-reported questionnaires’ scores and clinicians’ ratings. Only participants with a satisfying minimum within- and between-day compliance will be included in this analysis (i.e., at least 5 EMA questionnaires filled). We will observe associations between: the global EMA index and the overall score of the HADS; the depression EMA index with the BDI score, the HADS depression subscale score and the MADRS score; the anxiety EMA index with the HADS anxiety subscale score and the HAM-A.

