## Discussion

### Anticipated Results

#### Primary Objective

A participation rate at inclusion between 75 and 90% is expected regarding previous results with EMA method (Johnson et al., 2009a,b). The completion rate of EMA questionnaires is expected to be at least of 80% for the entire group during each phase (Sibon et al., 2012). In order to have satisfying validity, correlations between EMA indexes and data collected using other methods are expected to be higher than 0.70.

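### The validity analysis pairs each "specific" EMA index only with scales of its own construct, so correlations above 0.70 can show convergence but not specificity

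*Protocol article*

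**What the plan says.** The section on outcomes and statistical methods for the primary objectives defines three indexes. The broadest pools every EMA symptom, which the section counts as 11. For depression, six items are named: "a specific depression index (including sadness, anhedonia, fatigue, concentration difficulties, negative thoughts, pessimism"). For anxiety there are five, given as "a specific anxiety index (including anxiety, agitation, physical tension, irritability, concentration difficulties"). Concentration difficulties is in both of the last two.

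The same section names every pairing to be correlated. The global index goes with the HADS total. The depression index is paired in "the depression EMA index with the BDI score, the HADS depression subscale score and the MADRS score". The third pairing is "the anxiety EMA index with the HADS anxiety subscale score and the HAM-A". No index is paired with a scale of the other construct, and the correlation between the two indexes is not mentioned.

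The benchmark is under Anticipated Results, Primary Objective: for validity to be satisfying, "correlations between EMA indexes and data collected using other methods are expected to be higher than 0.70".

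Table 1 gives the timing. BDI-II, HADS and EMA are taken at discharge (phase 1b), 2 months (phase 2) and 4 months (phase 3). MADRS and HAM-A are taken in hospital (phase 1a) and at 4 months only.

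**The concern.** An index described as specific to depression should follow depression scales more closely than anxiety scales. The plan looks at only one side of that comparison. A high correlation with the BDI is what a good depression index would give, and also what a general distress score would give. The listed pairs cannot separate the two.

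The question matters in this population by the authors' own account. The background says that signs of stroke can mimic or hide depressive and anxious symptoms. It reports that some acute symptoms predict later depression, "whereas symptoms such as fatigue, apathy and concentration difficulties do not". The anticipated results describe fatigue, physical tension and attention difficulty as physical and non-specific. So two of the six depression items (fatigue, concentration) and two of the five anxiety items (physical tension, concentration) are symptoms that the article itself treats as non-specific.

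At stake is the wording of a primary conclusion. The study could report two valid specific EMA measures when its evidence supports only that each one rises and falls with established scales.

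**Working it through.** **Inputs from the article.** The depression index has 6 items, the anxiety index 5, and 1 is shared, so there are 6 + 5 − 1 = 10 distinct symptoms. The content section also lists 10: "sadness, anhedonia, fatigue, diminished concentration ability, negative thoughts on oneself, pessimism, anxiety, psychomotor agitation, physical tension, irritability". (The stated total of 11 equals 6 + 5 with the shared item counted twice. That is a separate inconsistency.) The benchmark is r > 0.70. The expected analysable number reproduces: 40 × 0.75 = 30 and 40 × 0.90 = 36.

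**Assumed inputs.** The article gives no item or scale loadings. Item loadings λ of 0.6 to 0.8, plus an inter-item correlation of 0.30 (λ = √0.30 = 0.55), and scale loadings L of 0.75 to 0.90 are assumptions.

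**Model with no specificity.** Every item loads λ and every scale loads L on one distress factor. The sum of k items has variance S(k) = k²λ² + k(1 − λ²), and its correlation with any scale is L × kλ/√S(k). This expression does not depend on whether the scale measures depression or anxiety, so own-construct and cross-construct correlations are identical.

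- λ = 0.7, L = 0.80. Depression index: 0.80 × 4.2/√20.70 = 0.739. Anxiety index: 0.80 × 3.5/√14.80 = 0.728. Both exceed 0.70.
- Inter-item r = 0.30, L = 0.80. Depression index: 0.80 × √(1.8/2.5) = 0.679. Anxiety index: 0.80 × √(1.5/2.2) = 0.661. Both fall short.

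Expected correlations (depression index / anxiety index) over the range:

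| Item loading | L = 0.75 | L = 0.80 | L = 0.85 | L = 0.90 |
|---|---|---|---|---|
| 0.55 (r = 0.30) | 0.64 / 0.62 | 0.68 / 0.66 | 0.72 / 0.70 | 0.76 / 0.74 |
| 0.6 | 0.66 / 0.64 | 0.70 / 0.69 | 0.75 / 0.73 | 0.79 / 0.77 |
| 0.7 | 0.69 / 0.68 | 0.74 / 0.73 | 0.79 / 0.77 | 0.83 / 0.82 |
| 0.8 | 0.72 / 0.71 | 0.77 / 0.76 | 0.81 / 0.81 | 0.86 / 0.85 |

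**Sampling at N = 30 and 36.** In 8,000 simulated studies under this model, all five listed own-construct correlations exceeded 0.70 in 28% and 30% of studies at λ = 0.7, L = 0.80, and in 76% and 80% at λ = 0.8, L = 0.85. Each index passed on at least one of its scales in 76% and 78% at the first setting, and in 97% and 98% at the second.

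**Contribution of the shared item.** If all items were otherwise uncorrelated, the overlap alone would give r = 1/√(6 × 5) = 0.18 between the indexes. Under the one-factor model with λ = 0.7, the indexes correlate (30 × 0.49 + 0.51)/√(20.70 × 14.80) = 0.87 with the item. They correlate (20 × 0.49)/√(14.80 × 9.88) = 0.81 with it removed from both. At inter-item r = 0.30 the values are 9.7/√(15 × 11) = 0.76 and 6.0/√(11 × 7.6) = 0.66. The item adds 0.06 and 0.10 in these two cases, and 0.04 at λ = 0.8. Most of the correlation remains without it.

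**Precision of an own-versus-cross comparison.** By Fisher's z, an observed r of 0.70 has a 95% interval of about 0.45 to 0.85 at N = 30 and 0.48 to 0.84 at N = 36. Suppose an index is truly specific, with own-scale r of 0.75, cross-scale r of 0.60 and scales correlated 0.6 to 0.7 (all assumed). A dependent-correlation test then detects the difference with power of about 26–32% at N = 30 and 31–38% at N = 36.

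**The case against.** The best defence is that the study never set out to test discrimination. The abstract describes validity as a comparison of EMA with conventional measures. Beside a global index, specific may mean no more than a subset of symptoms, and 0.70 is an expectation in the Discussion, not a formal test. Items were adapted from the MINI depression and anxiety modules, so a shared symptom can be defended diagnostically. Secondary objective 4 relates single EMA symptoms to both depression and anxiety ratings. The article also condenses a fuller protocol.

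Much of this stands, and it limits the point to what the validity analysis can conclude. It does not remove it. The article itself fixes the item lists, the pairings and the benchmark, so this is not a detail left open. Objective 4 works symptom by symptom, lies outside the validity assessment and does not set either index against the other construct.

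Several stronger readings are tempting but not supported:

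- That faulty indexes would carry into objectives 4 and 5. Both use single symptoms, not the indexes.
- That the study would recommend the indexes for screening. The clinical implications only suggest further research to develop an instrument.
- That all scores are taken at the same visits. All scales and EMA coincide only at phase 3.
- That the background shows fatigue and concentration to be invalid items. It concerns prediction of later depression in general stroke populations and leaves minor stroke as an open question.
- That both indexes would pass 0.70 whatever they measure. This depends on the assumed loadings.

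**Conclusion.** The point holds as a limit on the primary validity conclusion. The listed correlations can support convergent validity only; they cannot show that either index is specific. Under a single distress factor both indexes can pass 0.70 with no specificity at all (0.74 and 0.73 at item loading 0.7 and scale loading 0.80), but weaker assumed loadings put both below it. The possibility therefore rests on unverified loadings, whereas the equality of own-construct and cross-construct correlations under one factor does not depend on their size. The absent cross-construct comparison is the main defect, and removing the shared item alone would not cure it. No planned analysis becomes wrong. The change is worth making because validity is part of the primary objective and the data are already collected.

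**What to change.** In the primary-objective methods, keep the listed pairs and add:

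1. The cross-pairs: depression index with HADS-A and HAM-A; anxiety index with BDI, HADS-D and MADRS.
2. The correlation between the two indexes.
3. Use of scales taken in the same phase as the EMA week. Phases 1b and 2 allow the HADS and BDI pairs; only phase 3 allows all of them.
4. Own-minus-cross differences with confidence intervals and no pass/fail rule for relabelling an index. At N = 30 to 36 such a rule would often mislabel a truly specific index.
5. A sensitivity table with concentration difficulties removed from both indexes and fatigue removed from the depression index.
6. A statement that the conclusion is limited to convergent validity unless these estimates support specificity.

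The cost is small: 4 extra correlations at each of phases 1b and 2 (three cross-pairs and the index pair) and 6 at phase 3 (five cross-pairs and the index pair), so 4 + 4 + 6 = 14, plus the sensitivity table. The downside is a possibly less favourable validity statement.

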##### Outcomes and statistical methods for secondary objectives

(1) Frequency will be estimated as the ratio of depressed and anxious participants to the total number of participants. Presence of depression and anxiety will be determined in two different ways: according to the examination of psychiatric disorders during the semi-structured interview; and as a function of the cut-off scores of self-reported questionnaires and clinicians’ ratings scale previously reported in the instruments section.

(2) Univariate logistic regression analysis will be performed to study if the clinical variables (subtypes of anxiety and depression symptoms, coping strategies) predict depression and anxiety within each time and between times of the study.

(3) Descriptive analysis will be performed on clinical, sociodemographic and medical measures to describe depressed and anxious participants. Their results will be compared to healthy participants (presenting no significant depression and anxiety) with Chi-square and Student’s *t*-test.

(4) We will examine whether EMA of the different symptoms of depression and anxiety are associated with self-report and clinician-rated depression and anxiety to describe characteristics of PSD and PSA. Means-as-outcomes modeling will be used to describe those associations.

(5) In order to describe the time dynamics between anxiety and depression symptoms, coping strategies and contextual settings assessed with EMA, we will use a Multilevel Vector Autoregressive method (Bringmann et al., 2013). With the Vector Autoregressive (VAR) model, each variable at time point *t* is regressed to the time point *t* – 1 of every other variable. For example, sadness at 1 pm is regressed with all other depression and anxiety symptoms (including sadness) at 10 am. The multilevel-VAR model is suited to the hierarchical structure of EMA data and it enables to describe population dynamics as a function of within-person variability.

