### Objectives

This article aims to describe an innovative study design for the assessment and investigation during 4 months (following stroke), of minor stroke patients’ psychological health (depression, anxiety), coping strategies and quality of life combining classical standard scales and questionnaires with EMA using a smartphone application.

Primary objective is a methodological one. We aim to evaluate feasibility, acceptability, quality and reliability of data collected by EMA in minor stroke patients at different times and in different contexts during the first 4 months following a stroke.

Secondary objectives focus on studying psychopathological manifestations after stroke and the processes involved in their onset and evolution. Thus, we have several objectives considering these points: (1) to estimate the frequency and assess the evolution of anxiety and depression in minor stroke population, (2) to determine the risk factors and determinants of PSA and PSD in minor stroke patients and to study if coping is a reliable predictor, (3) to describe the clinical and psychosocial characteristics of depressed and anxious individuals after a minor stroke, (4) to describe symptomatic characteristics of PSD and PSA, (5) to study the sequences and dynamic processes between anxiety and depression symptoms, coping strategies and contextual and ecological factors at different times (during the first days, at 2 months and at 4 months) and contexts (hospitalization, discharge, return to work) after stroke.

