##### During hospitalization (phase 1a)

Each patient admitted to the Neurovascular Intensive Care Unit of the Paris Saint-Joseph Hospital Group for a stroke is screened by a physician for inclusion and non-inclusion criteria. The investigator, a psychologist, then meets eligible patients in order to explain the study and to give them an information letter containing the objectives and procedure. Patients who agree to participate sign the consent and then are assessed for depression and anxiety during a semi-structured interview.

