#### Variables and Instruments

##### Psychiatric symptoms and disorders

*The Mini International Neuropsychiatric Interview* (MINI) (Sheehan et al., 1998) is a structured diagnostic interview used for DSM-IV (American Psychiatric Association, 2000) psychiatric disorders assessment. This is one of the most used instrument for psychiatric disorders diagnostic and it has been translated and validated in several languages including French (Lecrubier et al., 1997; Sheehan et al., 1998). It is composed of several modules corresponding with specific psychiatric disorders from DSM-IV. We use modules related to mood disorders (Major Depressive Episode, Dysthymia) and anxiety disorders relevant in the context of stroke (Post-traumatic Stress Disorders, General Anxiety Disorder).

*The Montgomery and Asberg Depression Rating Scale* (MADRS) (Montgomery and Asberg, 1979) is an observer-rated scale for depression symptoms assessment. It is composed of 10 items. Each one corresponds with a depressive symptom and is rated from 0 to 6 depending on the intensity of the symptom in the individual assessed. The scale has been validated in French (Lempérière et al., 1984). We refer to a structured interview guide for the administration of this scale which reinforce interrater reliability (*r* = 0.93) (Williams and Kobak, 2008). A cut-off point at 8 has been determined for screening depression after a stroke (Sagen et al., 2009; Kang et al., 2013).

*The Hamilton Anxiety Rating Scale* (HAM-A) (Hamilton, 1959) is an observer-rated scale for anxiety symptoms assessment composed of 14 items rated from 0 to 4. We use a French version of the scale previously validated (Pichot et al., 1981) and we refer to a structured interview guide for the administration of the scale in order to optimize interrater reliability (Shear et al., 2001). A cut-off point at 8 has been determined for screening anxiety in numerous previous research (Ballenger, 1999; Matza et al., 2010).

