###### Medical condition and treatment

Data about the medical condition of the participants including previous and present affections (somatic, neurologic, psychiatric), family history neurological affections, medical treatment at hospital entrance, vascular risk factors (BMI, diabetes, cholesterol, high blood pressure, alcohol and other substance use).

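### Patients already depressed or anxious before the stroke can enter, and neither the case definitions nor the univariate risk-factor models separate persisting from new cases

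*Protocol article*

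**What the plan says.** - **Aim.** The Objectives section describes the secondary objectives as "studying psychopathological manifestations after stroke and the processes involved in their onset and evolution". Objective (2) asks for the risk factors of post-stroke depression (PSD) and post-stroke anxiety (PSA), with coping as the predictor of main interest.
- **Eligibility.** Among mental conditions, the inclusion and non-inclusion criteria name only dementia and psychotic disorder. Current or past depression or anxiety is no bar.
- **Case definition.** Outcomes and statistical methods for secondary objectives, item (1): "Frequency will be estimated as the ratio of depressed and anxious participants to the total number of participants". A case is identified either "according to the examination of psychiatric disorders during the semi-structured interview" or "as a function of the cut-off scores of self-reported questionnaires and clinicians’ ratings scale previously reported in the instruments section".
- **Timing.** In hospital (phase 1a), patients "sign the consent and then are assessed for depression and anxiety during a semi-structured interview". Table 1 places the MINI, MADRS and HAM-A at phase 1a and at 4 months (phase 3). The BDI-II, HADS and Brief-COPE start only after discharge (phase 1b) and are repeated at phases 2 and 3.
- **History.** Under Medical condition and treatment, the recorded data include "previous and present affections (somatic, neurologic, psychiatric".
- **Model.** Item (2) specifies univariate logistic regression of depression and anxiety on symptom subtypes and coping strategies, both within and between study times.

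**The concern.** The onset and risk-factor aims are about illness that appears after the stroke. The rule for counting cases takes everyone who is ill at the assessment, whenever the illness began. A patient who was depressed before the stroke, was depressed in hospital and is still depressed at 4 months has the same outcome value as one who became depressed in the third month.

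For a prevalence this does no harm. For a model that relates an earlier measurement to later caseness, it does. Existing illness shapes early symptoms and may shape coping, and it also tends to last. A symptom or coping strategy that merely marks existing illness would then look like a predictor of PSD or PSA. Coping is especially exposed. The Brief-COPE instructions are reworded to ask about stroke-related stress, and the scale is first given at phase 1b, after the phase 1a interview. For anyone already ill at that interview, the illness comes before the first coping measurement.

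**Working it through.** **1. The plan's own figure.** Sample Size gives 40 participants and 75 to 90% acceptance of the smartphone assessment: 40 × 0.75 = 30 and 40 × 0.90 = 36. This reproduces the stated 30 to 36. Patients who refuse the smartphone part still complete the questionnaires and interviews (Limitations), so case counts below use 40.

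**2. Following the rule as written.**

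| Patient | Ill at phase 1a | Ill at phase 3 | Counted at phase 3 under item (1) |
|---|---|---|---|
| Ill before the stroke, still ill | yes | yes | case |
| First ill in hospital after the stroke, still ill | yes | yes | case |
| First ill after discharge | no | yes | case |

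The three are indistinguishable in the outcome. A univariate model has the form logit P(case at later time) = a + b × (one earlier predictor). It has no place for phase 1a status or for history.

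**3. How persistence becomes prediction (constructed example, not an estimate).** Take 36 participants, 4 with persisting and 6 with new depression. The rule reports 10/36 = 27.8%; new cases among those at risk are 6/32 = 18.8%. Suppose a coping strategy is reported by half of the 32 at risk (16) and is unrelated to new illness (3 new cases in each half), while all 4 persisting cases report it.

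- Among the 32 at risk: 3/16 against 3/16, odds ratio 1.
- Among all 36: 7 cases and 13 non-cases with the strategy, 3 cases and 13 non-cases without it. Odds ratio = (7 × 13)/(13 × 3) = 2.33.

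The planned model reports the second figure.

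**4. How many cases could be affected.** Inputs from the article (Depression and Anxiety in Stroke Survivors): depression 20 to 40%, anxiety 18 to 32%. Pre-stroke prevalence q is not given and is assumed at 5 to 20%. It is also assumed that every pre-stroke case is still a case when counted. With observed rate p, pre-stroke share of cases = q/p and new cases = 40 × (p − q), with q capped at p.

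| Observed rate | Cases in 40 | q = 5% | q = 10% | q = 15% | q = 20% |
|---|---|---|---|---|---|
| Depression 20% | 8 | 25%; 6 new | 50%; 4 new | 75%; 2 new | 100%; 0 new |
| Depression 40% | 16 | 12.5%; 14 new | 25%; 12 new | 37.5%; 10 new | 50%; 8 new |
| Anxiety 18% | 7.2 | 28%; 5.2 new | 56%; 3.2 new | 83%; 1.2 new | 100%; 0 new |
| Anxiety 32% | 12.8 | 16%; 10.8 new | 31%; 8.8 new | 47%; 6.8 new | 62.5%; 4.8 new |

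Pre-stroke cases form a majority only if q exceeds p/2: above 10 to 20% for depression, above 9 to 16% for anxiety. The article does not say on which side of that line this population lies.

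**The case against.** The strongest reply is that objective (1) asks for frequency and evolution, and the article compares its expected frequency with published prevalences in stroke survivors. Current cases over all participants is the matching estimator. This stands in full: the ratio in item (1) is right for that objective and should not be replaced.

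A second reply is that the article condenses a fuller protocol, and that the repeated MINI and the recorded history already allow new cases to be identified. It is true that the data exist. But the article does state the case rule and the model, and a univariate regression over all participants leaves no room for baseline status. This is a method fixed in a way that does not fit the aim, rather than a missing detail.

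A third is that scale cut-offs offer a second case definition. They do, and item (2) does not say which definition feeds the regressions. Neither definition distinguishes persisting from new illness, so the choice does not matter for this point.

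Finally, these are secondary aims in a 40-person study whose primary objective is methodological. That limits the weight of the point but does not remove it.

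**Conclusion.** The concern holds for the onset and risk-factor aims. Pre-stroke depression and anxiety are not excluded, both case definitions pool persisting with new illness, and the between-times regressions do not condition on phase 1a status. Its size cannot be determined from the article. Under the assumed 5 to 20% pre-stroke prevalence, the share of cases that predate the stroke runs from 12.5% to 100%.

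Four stronger readings are tempting and are not supported:

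- **That most counted cases predate the stroke.** No figure in the article shows this; the table above neither establishes nor excludes it. In the constructed example the share is 4/10.
- **That the frequency objective is answered with the wrong cases.** It is a prevalence, and it is estimated as one.
- **That some MINI disorders cannot newly arise within 4 months.** This depends on the minimum durations of the diagnoses, which the article does not give. It would follow only for a module requiring more than 4 months.
- **That the in-hospital interview mainly describes the pre-stroke state.** The article gives neither its look-back nor its day. If the 2-week window stated for phase 3 applied there too (an assumption), the pre-stroke part would be (14 − d)/14 at day d: 86% at day 2, 50% at day 7 and 0% at day 14.

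**What to change.** **Item (1).** Keep the overall ratio as the frequency estimate. Also report, separately, cases already present at phase 1a (with and without recorded psychiatric history) and cases new after phase 1a, by MINI module and by scale cut-off. The MINI is not repeated at phase 2, and the BDI-II and HADS are not given at phase 1a. The split of self-report cases must therefore take phase 1a status from the MINI, MADRS or HAM-A.

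**Item (2).** For phases 2 and 3, run the between-times risk-factor models among participants free of the disorder at phase 1a, or adjust for phase 1a status, for example the MADRS or HAM-A score. Label these analyses exploratory.

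**What to avoid.** Do not call every phase 1a diagnosis pre-stroke illness, because reactions that began in hospital after the stroke would be misclassified. Do not rescore the general anxiety disorder module with a shortened duration; that would alter the diagnostic instrument.

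**Cost.** A few sentences and one derived variable, all from data already planned. Restriction leaves fewer participants and events in the onset analyses (0 to 14 new depression cases in 40 on the assumptions above). Adjustment keeps everyone but spends one covariate in a small model.
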